### Outcomes

Primary outcome measures will be the following:
Patient registrationPatient response to reminders: (a) *intention* to contact RetinaScreen, (b) have contacted RetinaScreen, (c) have attended a screening or (d) none of these. This will be verified through a phone call from the practice as part of the 6-month audit.Patient attendance at retinopathy screening, verified through a letter received by practices from the national screening programme, RetinaScreen. Patient attendance will be measured (via practice audit) at baseline and at 6 months.

Figure 3 shows the schedule of enrolment, interventions and assessments.

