Intervention has potential effect on screening uptake and demonstrates potential cost savings which are likely to outweigh the direct cost of implementing the intervention; specifically, the intervention (1) increases the absolute number of patients registered for diabetic retinopathy screening and (2) increases the absolute number of patients attending or intending to attend screening, measured descriptively	• Number registered for diabetic retinopathy screening based on practice audit data • Number attending or intending to attend based on practice audit data • Potential savings calculated based on cost of delivering intervention compared to control, and absolute increases in number attending or intending to attend	The TSC will judge whether the intervention has some positive impact and demonstrates cost savings.

^a^Continuation criteria are in place to facilitate the Trial Steering Committee (TSC) to assess whether it would be viable to progress to a full trial or whether this could be done following modifications to the trial protocol [50]. Continuation to the full trial will not occur unless problems can be overcome. Continuation criteria may be adapted, and supplementary data may be used to facilitate decision-making about whether to proceed to a full trial even when criteria have not been met

^b^To achieve 80% power to detect a change from 60 to 70% (*α* = 0.05), a total sample of 712 eligible patients would be needed. Assuming an average practice size of 1200 patients and a 5% prevalence of type 2 diabetes, at each practice, it is estimated that 12 patients would not be registered for the screening programme (20%). Of the 48 patients registered, 18 would be eligible (17 would be non-consenters (34%) and 1 would be a non-attender (3%)). Therefore, at least 40 practices would need to be recruited (20 per arm) for a full trial. To allow for a lower number of eligible patients per practice, we aim to recruit > 40 practices for the full trial

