If there is no evidence (e.g., letter) on the patient file to indicate they are registered with the national screening programme, the staff member will verify their status through the dedicated national telephone line or online portal. Practices will be asked to complete the first step of the audit within a maximum of one calendar month. Practices with large numbers of people with diabetes may not have the capacity to audit all their patients. Therefore, practices which have > 100 patients with diabetes will be asked to audit a random sub-sample of 100 patients. They will receive advice and support from the research team on this process. They will be asked to record the total number of patients with diabetes and retain a file with some basic demographic information (age, gender, type of diabetes) to examine whether the audited sub-sample is different from patients who were not sampled. The baseline audit will be completed within one calendar month of starting the trial. At 6 months, practices will re-audit eligible patients. As the 6-month period is insufficient for all patients to attend and receive a confirmation letter from RetinaScreen, practices will also verify their status via phone call, i.e., to determine whether they (a) intend to contact RetinaScreen, (b) have contacted RetinaScreen or (c) have attended the screening. If they do not fulfil (a), (b) or (c), then, they will be asked why, and this information is recorded on the audit file. Audit data will be made available to study researchers after it has been fully anonymised at the practice.

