##### Verbal reminders

All eligible patients will receive a phone call from a practice nurse, reminding them to attend the screening. Nurses who deliver the phone call will follow a short script (Additional file 2) and inform the patient they will receive a follow-up letter with more information. At this point, the patient status will also be updated on the audit file and electronic patient record, for example, if the patient is attending another service for screening (e.g., ophthalmologist). This will enable staff to shortlist patients who should receive the letter. In-person reminders will be delivered opportunistically by GPs and practice nurses if an eligible patient attends for an appointment during the 6-month trial period. They will follow the short script (Additional file 2) and provide patients with a standard information leaflet (Additional file 3).

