### Control practices

In control practices, data collection will be carried out at 6 months, using date-restricted data extraction from the electronic medical record to capture data for the full 12-month period prior to the intervention, so this includes baseline and 6 months of follow-up data. This will match the 6-month period in intervention practices, during which they will have acted as control practices. This will ensure we have comparative data collection prior to the delivery of the intervention to the control group on study completion. This approach was chosen as collecting data at baseline (i.e., 6 months before study start) would constitute an intervention in those practices; knowledge of non-attenders would lead to a change in usual care as the control group would likely follow-up patients immediately. Control practices will receive the same supports and training as intervention practices to facilitate the audit feedback loop.

Implementing the patient-level intervention will not require alteration to usual diabetes care (including the use of any medication). Usual care will continue for both trial arms.

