**Study procedures**		
4. Are the data collection processes, including mode and duration of data collection and outcome measures used, acceptable to staff?	Acceptability	**Qualitative:** staff interviews, any feedback on research processes during the study
5. Is the study feasible in terms of recruitment and retention procedures and data collection?	Feasibility	**Quantitative:** recruitment (level of interest) and retention rates, time taken to set up practices, conduct practice visits, deliver briefing/training and monthly phone calls **Qualitative:** any feedback on research processes during the study

As this is a pilot study, the level of missing data will be documented, but no imputation will be undertaken. As outlined, adherence to the study protocol (fidelity assessment) will be assessed throughout the trial period and at trial completion as part of the process evaluation. Exploratory descriptive analysis of the primary outcome will be conducted using the intention-to-treat approach.

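### The count of patients attending or intending to attend rests on a 6-month phone call that is not stated for control practices, so it can favour the intervention with no true effect

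*Protocol article*

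**What the plan says.** All references are to the protocol article.

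- **Outcomes.** The second primary outcome is the patient's response to reminders. Its categories are intention to contact RetinaScreen, then "have contacted RetinaScreen, (c) have attended a screening or (d) none of these". The source is given as "This will be verified through a phone call from the practice as part of the 6-month audit". The third primary outcome is attendance confirmed by a RetinaScreen letter held by the practice.
- **Audit and provide feedback.** "At 6 months, practices will re-audit eligible patients". Because 6 months is too short for every attendance to produce a letter, "practices will also verify their status via phone call, i.e., to determine whether they (a) intend to contact RetinaScreen", has made contact, or has attended. This text names no arm, but it sits in the description of the intervention's audit component.
- **Verbal reminders; GP-endorsed letter and information leaflet.** Eligible patients in intervention practices receive a nurse's reminder call and then a letter, well before the 6-month call.
- **Control practices.** There, "data collection will be carried out at 6 months, using date-restricted data extraction from the electronic medical record". The section explains that a baseline audit would itself change usual care, and it describes the resulting data as comparative. It mentions no outcome call.
- **Study design, Table 1.** One measure for the effect and cost-saving criterion is "Number attending or intending to attend based on practice audit data". The savings entry combines the cost of delivery relative to control with absolute increases in that same count.
- **Quantitative analysis.** The analysis is descriptive and exploratory, but an intervention effect is to be carried into the definitive trial's sample size.

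**The concern.** On a plain reading, the two arms contribute different things to one count. Intervention practices add stated intention and contact, collected by phone by the practice that sent the reminders. Control practices can contribute only what their records hold, which is in effect letters. A routine record would not normally show that a patient means to contact a screening programme, and control patients have had no reminder to respond to.

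The resulting difference would mix any real effect with a difference in measurement. It reaches three places: the steering committee's judgement of potential effect, the savings set against the cost of delivery, and possibly the effect size used to plan the definitive trial.

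**Working it through.** **1. The plan's own figure, for scale.** Table 1 (footnote b) plans the full trial to detect a rise from 60% to 70% with 80% power at α = 0.05, needing 712 patients. Two-sided, with pooled variance and no continuity correction:

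n per arm = [1.960 × √(2 × 0.65 × 0.35) + 0.842 × √(0.60 × 0.40 + 0.70 × 0.30)]² / 0.10² = 356, so 712 in total.

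The figure reproduces. The effect of interest in the full trial is therefore 10 percentage points.

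**2. Patients per arm.** The Sample size section expects 18 eligible patients among the 48 registered in each practice, so 4 × 18 = 72 per arm. If the 12 unregistered patients per practice also count, 4 × 30 = 120 per arm.

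**3. Expected gap with no true effect.** Let

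- a = letter-verified attendance, equal in both arms;
- r = share of the remaining patients reached by the 6-month call;
- q = share of those reached who state intention or contact (contact is taken here to count as intending).

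Intervention count: a + (1 − a) × r × q. Control count, with no call: a. Gap: (1 − a) × r × q.

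**4. Numbers.** The protocol gives none of these rates, so the ranges are assumptions: a 5–20%, r 50–90%, q 10–50%.

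| Case | a | r | q | Gap | Of 72 | Of 120 |
|---|---|---|---|---|---|---|
| Smallest | 20% | 50% | 10% | 0.80 × 0.50 × 0.10 = 4.0 points | 2.9 | 4.8 |
| Middle | 10% | 70% | 30% | 0.90 × 0.70 × 0.30 = 18.9 points | 13.6 | 22.7 |
| Largest | 5% | 90% | 50% | 0.95 × 0.90 × 0.50 = 42.8 points | 30.8 | 51.3 |

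In the middle case the arms read 28.9% and 10.0% although nothing has changed. That gap is larger than the 10 points the full trial is meant to detect. It vanishes only if no one reached by phone answers positively.

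**5. A before-and-after reading.** Table 1 speaks of absolute increases, so the criterion might be read as change within intervention practices. That does not remove the problem. No baseline measure of intention is described, so every positive answer at month 6 would count as an increase.

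**6. After the fix.** With letter-verified attendance alone in both arms, the expected gap under no true effect is a − a = 0.

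**The case against.** **Control patients may be called after all.** The audit section speaks of practices without naming an arm, control practices receive the same training and supports, and Figure 3 (the assessment schedule) was not available for this check. A reader might infer that the plan definitely measures controls from records alone. The text does not say that; it states no other source. This limits the certainty of the point but does not remove it, because the passages would still have to be reconciled.

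**The use is modest.** The analysis is descriptive, the effect criterion has no threshold, the committee has discretion, and letter-verified attendance is collected separately. In Table 1 the words about control attach to cost. All of this is fair, and there is no error rate to compute. But the committee is handed the combined count without a warning, and the control data are described as comparative.

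**Wider readings that the documents do not support.** A reader might infer three further faults:

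- *Baseline registration in controls cannot be recovered.* Nothing says that the portal or phone line returns current status only.
- *Patients found during the reminder call to be screened elsewhere leave the denominator.* The call does record "if the patient is attending another service for screening (e.g., ophthalmologist"), but its stated purpose is to decide who gets the letter, and the analysis is by intention to treat.
- *Patients not reached drop out.* The protocol says "the level of missing data will be documented, but no imputation will be undertaken", which fixes no complete-case denominator.

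**Letters alone lose information.** This stands. The calls exist because letters lag, and the fix has to accept that cost.

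**Conclusion.** The point holds in a limited form. As written, intention and contact have a stated source in the intervention arm and none in the control arm, yet Table 1 uses them to judge effect and savings. Under the assumed rates the combined count would favour the intervention by about 4 to 43 points with no true effect. The direction follows from the design; the size rests entirely on those assumptions.

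The conclusion depends on control patients not being called, which is the plain reading but is not stated outright. It does not touch letter-verified attendance, which record extraction can supply in both arms.

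**What to change.** **Change.** In Table 1, Control practices and Outcomes:

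- Base every between-arm comparison, the effect criterion and the savings figure on RetinaScreen letter-verified attendance within the same 6-month window, with all eligible patients as denominator in both arms.
- Use the same measure for any effect estimate carried into the definitive trial's sample size.
- Report intention and contact as an intervention-arm process measure only, with the number of patients not reached.

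**If control patients are to be called at 6 months before roll-out.** Say so consistently in Audit and provide feedback, Control practices and Outcomes, and rename the outcome so that it fits patients who received no reminder. Only then may the combined count be compared between arms. Even so, it remains a self-report to an unblinded practice.

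**Cost.** The main change is wording and needs no new data. Its drawback is that letters at 6 months undercount attendance, and not equally. Reminders start only after an audit of up to one month, so if they work, late letters would fall mainly in the intervention arm. The comparison would then be conservative, and the report should say so. The alternative would mean calling roughly 72 to 120 control patients (4 × 18 to 4 × 30).

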**Fig. 3 Fig3:**
[figure not shown]
Schedule of enrolment, interventions and assessment

### Sample size

As this is a pilot trial, formal sample size calculation has not been carried out [51]. The purpose of the pilot is to investigate the feasibility and acceptability of the intervention and study procedures with a view to adapting these, if necessary, for a future definitive trial. Eight practices will be recruited. Based on previous work conducted by the research team, within a practice, it is expected that 20% of patients will not be registered. Of those who are registered, it is expected 34% will not have consented to the programme, and 3% will not have attended. Therefore, assuming an average practice size of 1200 patients and a 5% prevalence of type 2 diabetes, at each practice, it is estimated that 12 patients would not be registered for the screening programme (20%). Of the 48 patients registered, 18 would be eligible (17 would be non-consenters (34%) and 1 would be a non-attender (3%)).

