#### People with diabetes

Inclusion criteria include the following:
Aged 18 years or overHave diagnosed diabetes (type 1 or type 2)Are eligible to attend the national screening programme but have not attended the screening service (i.e., recently in the past 12 months or ever)

Individuals will be excluded if they have attended the DRS programme recently (i.e., in the last 12 months) or are known to be having retinopathy treatment.

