##### GP-endorsed letter and information leaflet

Following the phone call, patients will receive a reminder letter, recommending participation in the national retinopathy screening programme, together with key messages (Additional file 2). A copy of the consent and registration form developed by RetinaScreen, a freepost envelope, and the information leaflet will be included with the letter.

Reminders will be issued to patients during a 2-week period following the audit. During this time period, it will be specified that the practice should make a reasonable attempt (i.e., three attempted phone calls) to remind patients using the approaches outlined, after which the letter should be issued.

All materials have been designed to be understood by readers with low literacy, numeracy or both, with input from healthcare providers and patients. Materials have been reviewed by the National Adult Literacy Agency and the IDEAs Patient and Public Involvement (PPI) group.

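### The expected eligible yield of 18 patients per practice omits the 12 unregistered patients whom the inclusion criteria admit, so the 40-practice figure and the recruitment cut-offs aligned with it rest on an inconsistent input

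*Protocol article*

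**What the plan says.** **Who is eligible.** Under Recruitment of general practices, People with diabetes, the trial admits adults with type 1 or type 2 diabetes who "Are eligible to attend the national screening programme but have not attended the screening service (i.e., recently in the past 12 months or ever"). The only exclusions are attendance in the last 12 months and known retinopathy treatment. Registration with RetinaScreen is not mentioned in either list. The National screening programme section says that everyone with diabetes above age 12 is invited, and that people missed when the register was built have to be added by a GP or another healthcare professional.

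**What the planning figures count.** In Sample size, for an average practice of 1200 patients and 5% prevalence of type 2 diabetes, "it is estimated that 12 patients would not be registered for the screening programme (20" per cent). The next sentence reads "Of the 48 patients registered, 18 would be eligible (17 would be non-consenters (34%) and 1 would be a non-attender (3" per cent). Footnote b to Table 1 repeats both figures.

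**What is built on them.** Footnote b begins "To achieve 80% power to detect a change from 60 to 70% (*α* = 0.05), a total sample of 712 eligible patients would be needed" and concludes "Therefore, at least 40 practices would need to be recruited (20 per arm) for a full trial". It is attached to the recruitment measure in Table 1, where fewer than 40 responding practices is red, 40 to 50 is amber and more than 50 is green.

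**How the unregistered figure elsewhere.** Patient registration is the first primary outcome listed. One of the effect criteria in Table 1 is that the intervention "increases the absolute number of patients registered for diabetic retinopathy screening". The reminder letter encloses "A copy of the consent and registration form developed by RetinaScreen".

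**The concern.** The word eligible covers two different groups. In the inclusion criteria it covers any adult with diabetes who can use the programme and has not attended. In the planning figures it covers only registered patients who have not consented or not attended. An unregistered adult who has never been screened belongs to the former group but not the latter, and the protocol expects 12 such patients in each practice.

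The pilot's own size does not depend on this; eight practices were chosen on available resources. What depends on it is the planning for the full trial. The number of practices needed is patients required divided by yield per practice, so a wrong yield carries straight through to the 40 in footnote b. The boundary between red and amber in the recruitment criterion is also 40, so a go/no-go threshold for the Trial Steering Committee is aligned with a count that the inclusion criteria contradict.

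**Working it through.** **Inputs from the protocol (Sample size; Table 1, footnote b).** Practice size 1200; prevalence 5%; unregistered 20%; among the registered, 34% non-consenters and 3% non-attenders; 60% versus 70%; 80% power; α = 0.05; 1:1 allocation. Sidedness and formula are not stated.

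**1. Reproduce 712.** Two-sided test of two proportions, pooled variance under the null, no continuity correction, mean proportion 0.65:

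n per arm = [1.960 × √(2 × 0.65 × 0.35) + 0.842 × √(0.6 × 0.4 + 0.7 × 0.3)]² / 0.10² = 355.9, so 356 per arm and 712 in total. This matches exactly. The formula has no term for clustering.

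**2. Reproduce 18 and 40.**
- Patients with diabetes: 1200 × 0.05 = 60
- Unregistered: 60 × 0.20 = 12; registered: 60 − 12 = 48
- Registered and not consenting or not attending: 48 × (0.34 + 0.03) = 17.76, stated as 18
- Practices: 712 / 18 = 39.6, rounded up to 40

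The 40 therefore comes from 18 as the whole yield. The 12 unregistered patients do not enter it.

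**3. Apply the inclusion criteria to the same rates.** 12 + 18 = 30 eligible per practice, which is 30/18 = 1.67 times the stated number; the unregistered are 12/30 = 40% of the group. Over the eight pilot practices that is 8 × 30 = 240 rather than 8 × 18 = 144 (neither total is stated in the protocol). Footnote b's own division becomes 712 / 30 = 23.7, or 24 practices.

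**4. Add clustering.** The protocol gives no intracluster correlation (ICC), so the values below are assumptions. With equal practice sizes, design effect DE = 1 + (m − 1) × ICC, and practices = 2 × (356 × DE / m, rounded up).

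| Assumed ICC | DE, m = 18 | Practices, m = 18 | DE, m = 30 | Practices, m = 30 |
|---|---|---|---|---|
| 0 | 1.00 | 40 | 1.00 | 24 |
| 0.01 | 1.17 | 48 | 1.29 | 32 |
| 0.02 | 1.34 | 54 | 1.58 | 38 |
| 0.05 | 1.85 | 74 | 2.45 | 60 |
| 0.10 | 2.70 | 108 | 3.90 | 94 |

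**5. What 24 or 40 practices of 30 patients would deliver.** Using the same formula, with effective patients per arm = practices per arm × 30 / DE:

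| Assumed ICC | Power, 24 practices | Power, 40 practices |
|---|---|---|
| 0 | 80% | 95% |
| 0.01 | 70% | 89% |
| 0.02 | 61% | 83% |
| 0.05 | 43% | 64% |

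The two omissions pull in opposite directions. Leaving out the unregistered inflates the practice number; leaving out the design effect deflates it. With 30 patients per practice, 40 practices is about enough at an ICC of 0.02 and well short at 0.05.

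**The case against.** **The unregistered are not left out of the pilot itself.** A reader might infer that the registration outcome has nobody in whom it can change. The protocol does not support that. The audit starts from the practice's own patients with diabetes, has a class for patients with no record, and requires their status to be verified with the programme. All eligible patients are then called and written to, and the letter carries the registration form. The 18 is an expected yield, not an operating definition. This part of the objection stands in full.

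**Reach, workload and cost are measured, not taken from 18.** A reader might also infer that the reach denominator or the cost per practice is wrong. Staff record the actual number eligible at baseline, the delivery measure uses audit data, time and resources are collected in monthly calls, and no reminder workload per practice is stated. This also stands.

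**The figure is provisional and errs on the safe side.** The pilot is meant to supply parameters for the full trial, and note a to Table 1 lets the criteria be adapted. Footnote b aims for more than 40 practices. This stands in part. The figure can be revised, but until it is, the threshold in force matches a number whose input conflicts with the inclusion criteria. The margin above 40 is there for lower yields, so it does not address this. The error is conservative only while clustering is ignored.

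**Thirty is not established either.** The 5% covers type 2 only, although type 1 is included. Patients who attended in the past but not recently are not clearly counted. Some unregistered patients may be in treatment or screened elsewhere. This stands: 30 is what the protocol's own rates imply, and the true yield could be lower or higher.

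**Conclusion.** The inconsistency is real and confined to the planning figures. On the protocol's own rates the inclusion criteria imply about 30 eligible patients per practice, while Sample size and footnote b use 18. The statement that at least 40 practices are needed rests on the 18. The cut-offs of below 40, 40 to 50 and above 50 are aligned with that figure; the protocol does not spell out their derivation, but the footnote is attached to the measure and the boundary coincides.

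The tempting conclusion is that 24 practices would do. The documents do not support it: 712 is a sample size for individually randomised patients and the full trial is to randomise practices. The size of the net error depends on an ICC that the protocol does not give. Over assumed values from 0.01 to 0.10, the requirement at 30 per practice runs from 32 to 94, against 48 to 108 at 18. These figures assume equal practice sizes and the stated 60% versus 70% contrast.

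**What to change.** - In Sample size and in footnote b, state that unregistered adults who meet the inclusion criteria count as eligible, and restate the expected yield as about 30 per practice (12 unregistered, 17 registered non-consenters, 1 registered non-attender). Note that it is approximate, because type 1 patients and lapsed attenders are not clearly counted and some unregistered patients may be in treatment or screened elsewhere.
- Re-derive the practice number in footnote b from that yield together with a design effect over a stated ICC range. Do not change one input without the other.
- Reset the recruitment cut-offs in Table 1 from the result, or say on what other ground 40 and 50 are kept.

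The cost is restated planning figures. The pilot's eight practices, the audit and the measured reach stay as they are, and the audit already establishes registration status.
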